### Sample size calculation

2.3

This three-arm randomized controlled trial will adopt an allocation ratio of 1:1:1. The primary outcome will be the change in fasting serum triglyceride (TG) levels from baseline to the end of the intervention. The main effect to be tested will be the difference in TG level changes between the omega-3 PUFA-enriched eggs intervention group and the regular eggs group. Based on previous dietary intervention studies in populations with metabolic syndrome, the estimated standard deviation of fasting serum TG is approximately 58 mg/dL (baseline TG level: 140.9 ± 58.0 mg/dL) (19). Sample size estimation will be based on data from a prior randomized trial, which reported a 35 mg/dL difference in triglyceride (TG) levels between participants consuming omega-3 PUFA-enriched eggs (152.476 mg/dL) and those consuming regular eggs (187.333 mg/dL) (20). Accordingly, the minimal clinically meaningful difference (δ) will be set at 35 mg/dL. Assuming a two-sided significance level of 0.05 and 80% statistical power (1–β = 0.80), the required sample size will be computed using the standard formula for comparing means between independent groups:

$$\begin{array}{l} N=\frac{2{\left(Z_{1-\frac{\alpha }{2}}+Z_{1-\beta }\right)}^{2}}{\delta^{2}} \end{array}$$

Where Z_1−α/2_ = 1.96, Z_1−β_ = 0.84, σ = 58 mg/dL, and δ = 35 mg/dL. Consequently, to meet the statistical power requirements for the primary comparison, approximately 44 participants per group will be needed. Considering a potential dropout rate of approximately 25% in 12-week dietary intervention studies among elderly populations (21), the sample size will increase accordingly:

$$\begin{array}{l} n=\frac{44}{1-0.25}\approx 59 \end{array}$$

Therefore, the final target sample size will be set at 60 participants per group, yielding a total of 180 participants across the three arms.

### Study participants

2.4

Participants will be recruited from Guangyang District, Langfang City, Hebei Province, using purposive and convenience sampling methods. Recruitment strategies will include community health clinic screenings, health education sessions, and telephone invitations.

Inclusion Criteria: Community-dwelling adults aged ≥ 65 years with a clinical diagnosis of MetS will be included. MetS will be defined as meeting at least three of the following five criteria: (i) abdominal obesity: waist circumference ≥90 cm (men) or ≥85 cm (women); (ii) hyperglycemia: fasting plasma glucose ≥6.1 mmol/L or 2-h post-load glucose ≥7.8 mmol/L on oral glucose tolerance test (OGTT), or previously diagnosed diabetes currently under treatment; (iii) elevated blood pressure: systolic blood pressure ≥130 mmHg and/or diastolic blood pressure ≥85 mmHg, or previously diagnosed hypertension currently under treatment; (iv) hypertriglyceridemia: fasting triglycerides ≥1.70 mmol/L; and (v) low high-density lipoprotein cholesterol: fasting HDL-C < 1.04 mmol/L.

Exclusion criteria: (i) medical conditions—severe hepatic or renal impairment, immunodeficiency disorders, active infectious diseases, type 1 diabetes, malignant hypertension, malignancy, thyroid dysfunction, electrolyte disturbances, acute diabetic complications or severe chronic complications (including cardiovascular or cerebrovascular events within the preceding month), prior bariatric surgery, or recent significant weight change (>5% over 3 months or >10% over 6 months); (ii) dietary factors—adherence to specialized therapeutic diets or substantial dietary modification within 12 weeks prior to enrollment; (iii) cognitive and functional status—severe medical or psychiatric disorders, or cognitive, visual, or hearing impairments that would preclude study compliance; (iv) medication and supplement use—current use of omega-3 PUFA supplements or medications known to affect lipid metabolism (concomitant medication use will be systematically documented during the screening visit via a comprehensive medication questionnaire); and (v) allergies—documented egg allergy.

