**Key inclusion and exclusion criteria**	Inclusion Criteria: Community-dwelling adults aged ≥65 years with a clinical diagnosis of metabolic syndrome. Exclusion Criteria: Medical Conditions: Severe hepatic or renal impairment, immunodeficiency disorders, active infectious diseases, or type 1 diabetes; malignant hypertension, malignancy, thyroid dysfunction (hyperthyroidism or hypothyroidism), or electrolyte disturbances; acute diabetic complications or severe chronic complications, including cardiovascular or cerebrovascular events, within the preceding month; prior bariatric surgery or recent significant weight change (unintentional or intentional loss >5% over 3 months or >10% over 6 months). Dietary Factors: adherence to specialized therapeutic diets (e.g., gluten-free for celiac disease) or any substantial dietary modification within 12 weeks prior to enrollment. Cognitive and Functional Status: severe medical or psychiatric disorders, or cognitive, visual, or hearing impairments that would preclude study compliance. Medication and Supplement Use: current use of omega-3 PUFA supplements (fish oil, omega-3 fatty acids, DHA, EPA, or ALA) or medications known to affect lipid metabolism. Concomitant medication use is systematically documented during the screening visit via a comprehensive medication questionnaire, capturing all prescription and over-the-counter drugs and supplements, including product names and duration of use. Allergies: documented egg allergy.

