### Community screening and enrollment

3.1

Eligible participants will be identified through screening of physical measurements and blood test data extracted from community health records. Potentially eligible individuals will be contacted by telephone and invited to an in-person information session, during which the study objectives, procedures, benefits, and risks will be explained in detail. Written informed consent will be obtained from all participants prior to any study procedures. Subsequently, trained researchers will administer structured questionnaires to assess baseline dietary intake, medical history, concomitant medications, and nutritional supplement use. Final eligibility will be determined based on strict application of predefined inclusion and exclusion criteria.

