### Universal study requirements and adherence promotion strategies

3.3

Consumption of deep-sea fish oil and other omega-3 fatty acid supplements is prohibited for the duration of the trial.

Strategies to enhance intervention adherence will mainly include the following: (1) Ensuring timely supply and accessibility of eggs. Eggs will be delivered weekly to the dining center of the community health service center (CHSC) nearest to the participants. For elderly participants who cannot collect eggs daily from the CHSC, eggs will be mailed or delivered to their homes on a weekly basis. These measures will prevent adherence interruptions caused by delayed delivery of the intervention eggs. (2) Ensuring appropriate cooking methods. Eggs will be boiled or steamed daily at the CHSC dining center, and elderly participants will collect and consume them every morning. For participants receiving home delivery, instructions on boiling or steaming eggs will be included with each delivery, reminding them to use these methods rather than frying or other cooking methods. (3) Targeted reminders and supervision. Each elderly participant will be assigned a researcher responsible for follow-up and reminders. Reminders will be delivered via telephone follow-up (once weekly) combined with smartphone/WeChat messages (daily timed push notifications). Traditional telephone reminders will be retained for those unfamiliar with smart devices. Family members or primary caregivers living with the elderly participants will be invited to participate in “monitor” training to assist with reminders and daily observation. A consumption log will be provided, and participants will check off each date upon consuming one egg, creating a visual completion prompt. (4) Implementing behavioral interventions and incentives. Participants will be instructed to consume eggs at breakfast to leverage the regularity of breakfast habits and improve execution stability. Participants will be provided feedback on changes in relevant biomarker levels (e.g., Omega-3 Index) to enhance motivation through biomarker visualization. Participants will be allowed flexibility in scheduling consumption within a week (e.g., consuming on Thursday if missed on Wednesday), but strict prohibition against consuming ≥2 eggs in a single sitting will be enforced to avoid overconsumption.

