### Plasma omega-3 PUFA as biomarkers

5.2

In this study, plasma omega-3 PUFAs will serve as objective biomarkers of intervention exposure, reflecting changes in participants' omega-3 intake and absorption, and enabling assessment of their relationship with metabolic outcomes. Samples will be collected at baseline (Week 0) and at Weeks 4, 8, and 12 of the intervention, coinciding with primary follow-up visits. Fasting venous blood samples will be collected, and plasma will be separated and stored at −80 C until analysis. Plasma concentrations of DHA, EPA and ALA will be quantified. Results will be expressed as absolute concentrations and, if necessary, as percentages of total fatty acids to facilitate inter-individual comparisons (22). Total lipids will be extracted from plasma using standardized procedures and quantified by gas chromatography (GC-FID or GC-MS) or liquid chromatography-tandem mass spectrometry (LC-MS/MS). Internal standards and quality control samples will be included in each assay batch to ensure consistency (23). These measurements will validate enhanced *in vivo* omega-3 exposure in the omega-3 PUFA-enriched egg group relative to the standard egg group, supporting subsequent pathway analyses of the “omega-3 exposure (DHA/EPA/ALA changes)–metabolic phenotype (e.g., TG)–omics signatures” relationship (24, 25).

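### The omega-3 supplement and lipid-drug exclusion covers current use only, with no look-back, so recent stoppers can enter and add avoidable noise to the TG contrast and the plasma omega-3 biomarker

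*Protocol article*

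**What the plan says.** The criterion appears twice in the protocol article. Section 2.4(iv) excludes "current use of omega-3 PUFA supplements or medications known to affect lipid metabolism". Table 1 (section 2.2) has "current use of omega-3 PUFA supplements (fish oil, omega-3 fatty acids, DHA, EPA, or ALA) or medications known to affect lipid metabolism". Both look only at use at the time of screening.

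Other items in the same lists look backwards. Section 2.4(ii) excludes "adherence to specialized therapeutic diets or substantial dietary modification within 12 weeks prior to enrollment", and Table 1 likewise has "any substantial dietary modification within 12 weeks prior to enrollment". Weight change is judged over 3 and 6 months, and cardiovascular or cerebrovascular events over one month.

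Under section 3.1, candidates are telephoned, attend an information session and consent; after that, "trained researchers will administer structured questionnaires to assess baseline dietary intake, medical history, concomitant medications, and nutritional supplement use". Table 1 says the screening questionnaire records product names and duration of use. It does not mention a stop date.

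Once a participant is in the trial, section 3.3 applies: "Consumption of deep-sea fish oil and other omega-3 fatty acid supplements is prohibited for the duration of the trial". Section 3 puts only a one-week baseline period before the 12-week intervention.

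The measurements affected are the primary outcome, which is the TG trajectory over weeks 0, 4, 8 and 12 (section 5.3), and the exposure measure, since "plasma omega-3 PUFAs will serve as objective biomarkers of intervention exposure" (section 5.2).

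**The concern.** The exposures closest to the primary outcome and to the biomarker are the ones without a look-back. Someone who stopped fish oil or a lipid-affecting drug shortly before the questionnaire can truthfully report no current use and be enrolled. If the effect of the stopped product is still wearing off, week-0 TG and plasma omega-3 are not at that person's steady level, and both may move during follow-up for reasons unrelated to the eggs.

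The primary analysis compares change over time, so a person-specific slope after week 0 goes into the outcome. Section 7 adjusts for baseline clinical parameters, which deals with differences in starting level but not with a slope that continues after week 0. The same movement affects the measure meant to confirm that enriched eggs raised omega-3 exposure. At stake are some power for TG and some clarity in the exposure check.

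**Working it through.** **1. The passages side by side.**

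| Item | Period covered | Where |
|---|---|---|
| Omega-3 supplements, lipid-affecting drugs | current use only | 2.4(iv), Table 1 |
| Dietary modification | 12 weeks before enrollment | 2.4(ii), Table 1 |
| Weight change | 3 and 6 months | 2.4(i), Table 1 |
| Cardiovascular or cerebrovascular events | preceding month | 2.4(i), Table 1 |
| Supplement ban | trial duration | 3.3, Table 1 |
| Baseline period before eggs start | 1 week | 3 |

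The dietary clause is a separate item from supplements and medication, so it does not clearly reach a stopped capsule and does not reach a stopped drug. No other section sets a wash-out.

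**2. The plan's own sample size.** Section 2.3 gives a difference of 35 mg/dL, SD 58 mg/dL, two-sided alpha 0.05, power 80% and dropout 25%.

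- n = 2 × (1.96 + 0.84)² × 58² / 35² = 2 × 7.84 × 3364 / 1225 = 43.06, so 44 per group.
- 44 / 0.75 = 58.7, so 59, set at 60. The plan's figures reproduce.
- Evaluable per arm: 60 × 0.75 = 45. Two-sample t power at 45 per arm is 80.8%.

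**3. Effect on TG.** Two inputs are assumptions because the document gives neither: the share p of entrants who recently stopped (5–20%) and their TG rebound R after week 0 (20–50 mg/dL). That the rebound falls inside follow-up is also assumed. A mixture of stoppers and others adds p(1−p)R² to the variance:

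SD′ = √(58² + p(1−p)R²), then t power at 45 per arm for 35 mg/dL.

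| p | R (mg/dL) | p(1−p)R² | SD′ | Power |
|---|---|---|---|---|
| 0 | – | 0 | 58.0 | 80.8% |
| 0.05 | 20 | 19 | 58.2 | 80.6% |
| 0.10 | 35 | 110.25 | 58.9 | 79.6% |
| 0.20 | 50 | 400 | 61.4 | 76.3% |

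Section 2.3 gives 58 mg/dL as the SD of fasting TG, not of its change. It is used here only because the plan used it as the planning SD; the relative inflation would differ with another SD.

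**4. Effect on the biomarker.** Section 3.2 gives 55.5 mg of DHA per enriched egg. Five eggs a week supply 55.5 × 5 / 7 = 39.6 mg/day on average. No EPA content is reported for the egg. The regular egg's DHA is not stated either, so the contrast between egg arms may be smaller. For scale, suppose a stopped supplement had supplied only the 250 mg/day of DHA plus EPA that section 3.2 quotes as the adequate intake (an assumption about the user). The amount withdrawn would then be 250 / 39.6, about 6 times the DHA that the egg supplies. The document gives no SD and no rate of decline for plasma omega-3, so this cannot be turned into a loss of precision.

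**The case against.** The strongest reply is that the harm is small and its mechanism undocumented. Nothing in the article gives wash-out kinetics, the share of volunteers who would have stopped recently, or the time between invitation and questionnaire. The Discussion (section 8) says compliance with traditional supplementation is generally low among Chinese populations, which points, indirectly, towards few recent users. The middle case costs about one point of power. The lowest figure needs one entrant in five to be a recent stopper with a rebound larger than the trial's own target difference. Some safeguards exist: medication is documented at screening, plasma omega-3 is measured at week 0, diaries track supplements and drugs, and baseline parameters are adjusted for. All of this stands and limits the importance of the point. None of it removes a slope continuing after week 0, and without a stop date recent stoppers may not be identifiable even for a sensitivity analysis.

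A reader might infer more than the document supports:

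- **Bias between the egg arms.** Randomisation spreads recent stoppers across arms in expectation. An average drift common to all arms cancels in the enriched-versus-regular contrast.
- **Chance imbalance as a further harm.** Unequal numbers of recent stoppers are the same variance component already counted in the power figures.
- **Twelve weeks as the right length.** That window was set for dietary change. Nothing in the article justifies it for every supplement and lipid-affecting drug.

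**Conclusion.** The point holds as a weakness in how the criterion is fixed. It is not an error in the sample size or a threat to the direction of the result. As written, the rule admits recent stoppers, and no other section closes the gap. Article condensation does not explain it, because the eligibility list is given in detail twice with windows on neighbouring items.

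The consequence is avoidable noise. For TG, the loss is about 0.2 to 4.5 points of power under the assumed shares and rebounds, and about 1.2 points in the middle case. The plan has little slack to absorb it, with 44 needed and 45 expected. For plasma omega-3 the size is unknown, but the small DHA dose makes it probably the more sensitive of the two. Severity is minor to moderate.

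**What to change.** Table 1 lists the trial as not yet recruiting, so the change can be made before anyone is enrolled:

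- In Table 1 and section 2.4(iv), replace current use with use within a stated look-back period before enrollment. The sponsor should choose and justify the length; the protocol's 12-week dietary window is one reference point.
- Add a stop date to the existing medication and supplement questionnaire, so that the criterion can be checked and recent users identified in analysis.
- State that the criterion applies to past use only and that nobody is asked to stop a treatment in order to qualify.

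The cost is one line of eligibility text and one questionnaire field. The downside is that a few recent users become ineligible.

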### Ethics

2.5

This protocol has been reviewed and approved by the Peking University Biomedical Ethics Committee (IRB00001052-25192) and will be conducted in accordance with the ethical principles of the Declaration of Helsinki. Prior to enrollment, eligible participants will be provided with comprehensive information regarding the study purpose, procedures, anticipated benefits, and potential risks. Written informed consent will be obtained from all participants before any study procedures commence. Signed consent forms will be maintained in secure, access-controlled storage.

## Study process

3

This study is designed as a community-based randomized controlled trial with a 12-week intervention period. Community-dwelling adults aged ≥ 65 years will undergo metabolic syndrome screening, including physical measurements and blood tests, to identify eligible participants based on predefined inclusion and exclusion criteria. A total of 180 participants will be enrolled and randomly allocated into three groups (60 per group) using a computer-generated randomization sequence. The total study duration will be 13 weeks, comprising a one-week baseline assessment period followed by a 12-week intervention. Follow-up evaluations and biospecimen collection will be conducted at weeks 4, 8, and 12 of the intervention, with the final assessment completed at week 13.

### Community screening and enrollment

3.1

Eligible participants will be identified through screening of physical measurements and blood test data extracted from community health records. Potentially eligible individuals will be contacted by telephone and invited to an in-person information session, during which the study objectives, procedures, benefits, and risks will be explained in detail. Written informed consent will be obtained from all participants prior to any study procedures. Subsequently, trained researchers will administer structured questionnaires to assess baseline dietary intake, medical history, concomitant medications, and nutritional supplement use. Final eligibility will be determined based on strict application of predefined inclusion and exclusion criteria.

### Three intervention groups

3.2

Omega-3 PUFA-enriched eggs group: Participants will consume one omega-3 PUFA-enriched egg daily, five days per week (Tuesday through Saturday) for 12 weeks. Participants will consume eggs uniformly in the morning to ensure intervention standardization. Monday and Sunday are designated as egg-free days, during which no eggs or egg-derived products are permitted. Eggs will be provided by a centralized supplier along with product quality inspection reports. Nutritional analyses for eggs used in the intervention and control groups will be conducted by the research team.

The omega-3 PUFA-enriched eggs used in this study were tested for nutritional composition by the Chengdu Food Quality Supervision and Inspection Institute in accordance with national standard methods. According to the first method specified in GB 5009.168-2016 (National Food Safety Standard: Determination of Fatty Acids in Foods), the total omega-3 content (sum of α-linolenic acid and docosahexaenoic acid) was 0.446 g per 100 g of eggs, including 0.335 g of α-linolenic acid (ALA) and 0.111 g of docosahexaenoic acid (DHA). Based on the first method of GB 5009.82-2016 (National Food Safety Standard: Determination of Vitamin A, D and E in Foods), the vitamin A content was 201 μg per 100 g and the vitamin E content was 4.41 mg per 100 g. Based on an edible portion of approximately 50 g per egg, each omega-3 PUFA-enriched egg provides approximately 0.223 g of total omega-3 fatty acids. According to the Chinese Dietary Reference Intakes (2023 Edition), the adequate intake (AI) of ALA for adults is 1,600 mg/day for men and 1,100 mg/day for women. The recommended adequate intake of DHA+EPA for adults is 250 mg/day, including 200 mg/day of DHA. Therefore, one omega-3 PUFA-enriched egg per day provides approximately 167.5 mg of ALA, accounting for 15.2% of the AI for women and 10.5% for men, and approximately 55.5 mg of DHA, accounting for 27.8% of the recommended adult intake, which can serve as an important dietary source of omega-3 fatty acids.

Regular eggs group: Participants will consume one regular egg daily, five days per week (Tuesday through Saturday) for 12 weeks. Participants will consume eggs uniformly in the morning to ensure intervention standardization. Eggs will be provided by a centralized supplier along with product quality inspection reports. Nutritional analyses for eggs used in the intervention and control groups will be conducted by the research team.

Blank control group: Participants will maintain their habitual dietary patterns throughout the 12-week study period.

In addition, during the subsequent intervention period, regular testing of omega-3 and other components in each group will be performed to verify and ensure that the intervention dose is clear and reproducible. This study will allow participants to consume other foods containing omega-3 fatty acids, provided that detailed records are maintained in dietary logs. Dietary intake will be assessed using the Food Frequency Questionnaire (FFQ) combined with 3-day 24-h dietary recalls. Participants will be required to provide particularly detailed documentation of omega-3-rich foods. During data analysis, these dietary records will be rigorously analyzed to evaluate their potential impact on the study outcomes.

